#### Random Allocation

A random number will be generated to recruit villages randomly within each arm. A statistician blinded to the study will generate random numbers for each arm of the study. Control arm and intervention arm villages are geographically distant and administratively exclusive, yet they are in the same province and similar demographically, socially, and culturally to evaluate social interventions.

#### Blinding

Double blinding is not possible. Participants are blind to the allocation. Participants and research assistants performing the assessment cannot know the random allocation to a cluster before the study begins. Bias and contamination are controlled.

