#### Care in Both Arms

In both arms, a basic health check, blood pressure check, and BMI assessment will be provided for the study participants. If any disease is suspected through the health check, appropriate referrals to existing health care services will be provided. This is considered a benefit for all study participants. The control group will receive the same assessment with an explanation that the assessment is being conducted as part of a survey and the result will be utilized for research purposes. They also receive the benefit of the additional health check followed by appropriate referrals to health care professionals. Control arm participants will receive usual care (ie, the current system of LTC common to all provinces in Thailand), consisting principally of a volunteer-assisted home care service in addition to traditional family-based home care. The differences between the 2 arms are the newly launched CIIC services, as described in the following sections.

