### Sample Size

A sample of 4000 community-residing older adults will be recruited, with 2000 adults in each arm of the study (control and intervention), which our calculations show should suffice for the power required by the study. Including 1500 participants in each arm should be ample to detect the effect size difference of 0.5 unit with an SD of 4 between the 2 arms. STATA version 11SE (Stata Corporation, College Station, TX) was utilized for sample and power estimations. The precision levels applied are a *P* value of .05 with a 95% confidence interval. The sample size is inflated (1) for a design effect of 1.2 for applying a cluster randomized design and (2) to compensate for potential nonresponses and drop-outs of up to 20% during recruitment and the study. After inflation, a total sample size of 4000 is estimated to be required for the study. Moreover, the sample size will be sufficient for the estimation of key parameters such as mean CBI, ADL, and health-related QOL indicators in the study population.

There will be 6 clusters in each arm. The cluster size is in the range of 300-350. Within each cluster, individual participants meeting eligibility criteria will be recruited consecutively. Informed consent will be requested from a representative of each cluster before randomization and from each older participant and a family caregiver after randomization.

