#### Data Collection and Follow-Up

Interviewer-administered, structured questionnaires will be used to collect the data. Follow-up will be comprised of (1) serial measurement of research outcomes, (2) monitoring the implementation for quality control, and (3) monitoring of serious adverse events related to the trial. Serial measurement of research outcomes will be applied, ensuring 6 months of follow-up for each participant. Baseline characteristics will be measured in both intervention and control arms before launching the CIIC service at the outset of the study. Postintervention, primary and secondary outcome measures will be measured again after 6 months of follow-up. There is minimal risk of drop-out from the study as the participants are long-term residents of the subdistricts.

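### The Blinding section says participants are blind and bias is controlled, but the services are open, consent follows randomization and the primary outcome is the caregiver's own interview rating

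*Protocol article*

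**What the plan says.** The Blinding section first concedes that double blinding cannot be done. It then states "Participants are blind to the allocation" and concludes "Bias and contamination are controlled". The only support it gives is: "Participants and research assistants performing the assessment cannot know the random allocation to a cluster before the study begins".

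Other sections of the protocol article bear on this:

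- **Sample Size:** "Informed consent will be requested from a representative of each cluster before randomization and from each older participant and a family caregiver after randomization". Within a cluster, "individual participants meeting eligibility criteria will be recruited consecutively".
- **Study Setting, Sequence Generation and Random Allocation:** one subdistrict is the intervention area and the other the control area. Random numbers only choose which villages are drawn within each.
- **Care in Both Arms:** the arms differ by the new CIIC services. Controls receive the same assessment "with an explanation that the assessment is being conducted as part of a survey".
- **Primary Outcome:** the caregiver's burden on the CBI at baseline and month 6 (24 items, 5-point Likert).
- **Data Collection and Follow-Up:** "Interviewer-administered, structured questionnaires will be used to collect the data". Baseline is taken in both arms before the CIIC service is launched.

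**The concern.** An open-label community trial is a legitimate design, and lack of blinding is not the fault here. The fault is that the article claims a protection the design cannot give, for an outcome that is sensitive to its absence.

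Two routes to bias follow. First, families are approached and consent when the arm of their area can already be known, so those who enrol may differ between arms. Second, caregivers who know they have had a respite service and training rate their own burden to an interviewer who can tell the arm from the subdistrict. A reader who takes the Blinding section at face value would discount both routes and read a small difference in CBI as an effect of the service.

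**Working it through.** **Step 1. Are participants blind?** The intervention consists of respite stays, caregiver training and group exercise twice a week (Care Capacity Building, Care Prevention Exercise Program, Registration). Families receiving these know it. Controls may be partly unaware of what the other subdistrict receives, but that does not make the statement true of participants in general.

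**Step 2. Can the section be read as pre-study allocation concealment?** What is unknown before the start is only which villages will be drawn. The arm of any drawn village is fixed by its subdistrict. Individual consent is sought "from each older participant and a family caregiver after randomization", so concealment does not cover enrolment of individuals either.

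**Step 3. Is the month-6 outcome protected?** The CBI is the caregiver's own rating, taken by interview. No blinding of respondent or interviewer at month 6 is described, and the subdistrict reveals the arm.

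**Step 4. What do the planned safeguards cover?** Baseline before launch (Data Collection and Follow-Up) keeps the service itself from altering baseline values. The random effects model (Statistical Methods) can adjust for measured differences between arms. Neither acts on how caregivers answer at month 6.

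**Step 5. How sensitive is the comparison?** No figure in the plan is in dispute, but its planning values give a scale.

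Inputs from Sample Size: difference 0.5, SD 4, alpha 0.05, design effect 1.2, loss 20%, 2000 per arm. Assumptions: two-sided test; 0.5 is in CBI points, which the section does not say.

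- Reproduction of the plan's figure: power is not stated. At 90%, n = 1345 per arm; 1345 × 1.2 = 1614; 1614 / 0.8 = 2018 after rounding up; total 4036, close to the stated 4000.
- The CBI total spans 24 × 4 = 96 points. The planning difference is 0.5 / 4 = 0.125 SD and 0.5 / 96 = about 0.5% of the span.
- Standard error: SE = 4 × √(2/n). For n = 1500, SE = 0.146. For an effective n = 2000 × 0.8 / 1.2 = 1333, SE = 0.155.
- With no true effect and a differential shift b, the false-positive rate is 1 − Φ(1.96 − b/SE) + Φ(−1.96 − b/SE).

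| Assumed shift b (points) | n = 1500 | n = 1333 |
|---|---|---|
| 0.1 | 10% | 10% |
| 0.2 | 28% | 25% |
| 0.25 | 40% | 37% |
| 0.3 | 54% | 49% |
| 0.5 | 93% | 90% |

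The values of b are assumptions; the documents give none. The table shows how little shift would matter, not how much shift there is.

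**The case against.** The strongest reply is that the section is badly worded rather than wrong in substance. It admits that double blinding is impossible, and saying bias is controlled is not saying it is absent. Challenges and Limitations admits possible baseline imbalance and asks for a baseline check. Baseline precedes launch, and confounder adjustment is planned. These points stand as mitigation of measured imbalance. They do not make participants blind or protect the month-6 rating, and the limitations text mentions neither open treatment nor consent after randomization.

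A second reply is that recruitment is close to a census. From the lower bounds in Study Setting, 18,000 × 18% / 10 = 324 older persons per intervention village, against 2000 / 6 = 333 needed per cluster. If villages are near that size, there is little room for selective enrolment. This tempers the enrolment route. It does not close it, because the population figures are lower bounds and Sample Size allows up to 20% nonresponse and drop-out.

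A reader might also infer several stronger things that the documents do not support:

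- *That consent explanations differ by arm.* Care in Both Arms ties the survey explanation to the assessment, not to consent, and the intervention arm's wording is not given.
- *That awareness campaigns drew burdened families into the trial.* The exercise section gives no timing of these campaigns relative to enrolment.
- *That the baseline shift can be calculated* from the 6.5% of older persons needing ADL help and the CBI threshold of 24. No CBI distribution by dependency is given. Setting 6.5% at 24 and everyone else at 0 implies an SD of 24 × √(0.065 × 0.935) = 5.9, which conflicts with the planned 4.
- *That selective enrolment would favour the intervention.* More burdened caregivers in that arm would raise its CBI and work against it in an unadjusted comparison.
- *That interviewers are CIIC staff.* Nothing says so; staffing detail may sit in the full protocol.

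**Conclusion.** The point holds as a misstatement with consequences. The two sentences in the Blinding section claim properties that the article's own account of services, areas, consent and outcome rules out. Reading them as pre-study concealment does not rescue them. Recruitment bias is possible but tempered by the early baseline, the planned adjustment and perhaps near-complete enrolment. Response bias at month 6 is open, and no planned analysis removes it.

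Neither bias can be sized from the documents, and the net direction is not determined. What can be said, if the planning values are in CBI points and a two-sided 5% test is used, is that a shift well below the 0.5-point planning difference would be enough to mislead. The wording should be corrected before results are reported. That the arm is fixed by subdistrict is a separate design matter; it is used here only because it makes the arm visible.

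**What to change.** 1. Replace the Blinding text with a statement that participants and providers are not blinded and that assessors can infer the arm from the subdistrict. Delete "Bias and contamination are controlled".
2. Report by arm the consent rate among those approached, and baseline CBI and ADL.
3. Adjust the month-6 CBI comparison for baseline CBI, within the random effects model already planned.
4. For any interviews still to be done, use one pool of interviewers working across both subdistricts, none of them CIIC staff or volunteers.
5. State residual recruitment and response bias in Challenges and Limitations.
6. For any further recruitment, use the same invitation and baseline script in both arms.

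Cost: items 1 and 5 are wording. Items 2 and 3 use baseline data the plan already collects, plus counts of families approached and refusing, which must be recovered if they were not logged. Item 4 costs some travel. Item 6 cannot help those already enrolled: the Results section says implementation ran to December 2020, with evaluation to finish by the end of March 2021.

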### Implementation

The details of the intervention are described in the Methods section (Figure 2). The overall study period is 2 years, which will allow a net intervention period of 6 months, with the remainder of the time spent on preparation for the study such as establishing the facility, recruiting human resources for the service and research implementation, and assessment and evaluation before and after the intervention (Figure 3).

**Figure 2 figure2:**
[figure not shown]
Activities and services in the intervention and control arms of the Community-Integrated Intermediary Care (CIIC) trial, Thailand.

**Figure 3 figure3:**
[figure not shown]
Timeline for the Community-Integrated Intermediary Care (CIIC) project, Thailand. C19: COVID-19 pandemic; P: PM 2.5 air pollution.

#### Data Collection and Follow-Up

Interviewer-administered, structured questionnaires will be used to collect the data. Follow-up will be comprised of (1) serial measurement of research outcomes, (2) monitoring the implementation for quality control, and (3) monitoring of serious adverse events related to the trial. Serial measurement of research outcomes will be applied, ensuring 6 months of follow-up for each participant. Baseline characteristics will be measured in both intervention and control arms before launching the CIIC service at the outset of the study. Postintervention, primary and secondary outcome measures will be measured again after 6 months of follow-up. There is minimal risk of drop-out from the study as the participants are long-term residents of the subdistricts.

#### Safety and Privacy Considerations

Confidentiality of data from the screening and intervention will be maintained by storing all paper-based patient material in locked cabinets accessible only to authorized personnel. Names or identity numbers of the patients will be excluded from the database. The databases are password protected and accessible only to authorized personnel and researchers. Participants will be informed that they are free to decide to leave the study without any impact on their privilege under the national health insurance.

### Ethics and Trial Registration

The research project has been approved by the World Health Organization (WHO) Ethical Review Committee (WHO/ERC ID; ERC.0003064) and Boromrajonani College of Nursing, Lampang Thailand Ethics Review Committee (E2562/005). It has been registered in the Thailand Clinical Trial Registry, with trial registration number TCTR20190412004.

### Statistical Methods

The analysis will follow the intention-to-treat analysis approach. Outcomes will be compared between intervention and control clusters after 6 months of intervention.

To assess the effectiveness of the intervention, the primary outcome, CBI, will be compared between intervention and control arms after 6 months of intervention. Depending on the nature of the variables, *t* tests, chi-square tests of cluster summary measures, or multivariate analyses will be applied. Data distribution and homogeneity will be checked and ensure the assumption of statistical tests. Cluster-level summary statistics will be compared. A random effects model will be applied to control possible confounders in individual and cluster levels.

The intervention in the CIIC trial is a complex intervention with several components of prevention, training, and service. It is basically empowerment of the community. Therefore, a village as a random effect is due to population and social economic status, and participation of the community is considered as source of variation.

To evaluate the impact of the intervention on the secondary outcomes (ADL for dependency, GDS for depression, and EQ-5D-5L for QOL), the analyses will compare the 2 arms by applying a multivariate analysis of variance model.

Afterwards, the cost of the intervention will be analyzed in terms of both the primary outcome and secondary outcomes. Statistical significance is defined as *P*<.05 with 95% confidence intervals.

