### Study Setting

Chiang Mai, Northern Thailand is the location of the study. There are 284,457 older adults in Chiang Mai city according to the 2019 provincial report. Older adults account for 18% of the population, which is higher than the national proportion of people ≥60 years old (16%). Chiang Mai is culturally similar to many neighboring ASEAN countries in terms of caring for older parents as a family tradition and social value.

Two subdistricts involved in the study, sub-district XXX (10 villages) for intervention and subdistrict YYY (15 villages) for control, are in the same Muang Chiang Mai district of Chiang Mai province. They are geographically distant from each other. They have similar demographic and sociocultural characteristics. Both subdistricts have a similarly sized population (>18,000 people), with similar aging rates (>18% of the population is >60 years old), according to local population statistics. People in both subdistricts are mostly Thai people who have access to health care services through the national health insurance system and social welfare services for older people covered by municipality funds.

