#### Screening and Assessment of Family Burden and LTC Capacity

After obtaining informed consent, screening of the families will be conducted to assess the capacity for and burden of caregiving for each family with older adults. All older adults and caregivers in each cluster who have provided informed consent will be screened for ADL status and health-related QOL utilizing the EuroQol 5-dimensions 5-levels (EQ-5D-5L) for older adults, and caregiver burden will be measured with the Caregiver Burden Inventory (CBI). The results will be utilized as a baseline assessment from which to measure the overall impact of the CIIC center.

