#### Primary Outcome

The primary outcome is the burden of family caregivers measured at a 6-month follow-up appointment. The CBI [14,15] will be applied to measure the family caregiver’s burden at baseline (month 0) and then again at month 6. CBI is an internationally well-validated measurement tool with a 24-item, 5-point Likert scale with the following 5 dimensions: time dependence burden (5 items), developmental burden (5 items), physical burden (4 items), social burden (5 items), and emotional burden (5 items).

The total scores will be summed, with total scores >36 indicating a risk of “burning out” whereas total scores >24 are considered indicative of “a necessity to seek some form of respite care.”

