#### Challenges and Limitations

Cluster randomization may increase the risk of imbalance in the 2 arms at baseline. This approach of randomization we practiced in CIIC may have limitations but would minimize the residual confounders caused by differences in characteristics of the municipalities. However, this is the best pragmatic approach for the current trial. The results of randomization should be checked carefully at baseline by comparing the aggregate-level summary.

We do not have data about the desirability of temporary, short residential stays at the CIIC facility for older adults and their families. We may have underestimated the demand and therefore, also the required resources. Researchers have consulted with local governments about the possibility of tapping into reserve capacity and resources. Social distancing measures in the COVID-19 pandemic delayed the activities, but we adhered to those measures to ensure the safety of participants.

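### The primary analysis is worded as a month-6 CBI contrast, with several analyses unranked and no stated role for baseline CBI, although each arm is one pre-assigned subdistrict

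*Protocol article*

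**What the plan says.** On the primary analysis, Statistical Methods states that "the primary outcome, CBI, will be compared between intervention and control arms after 6 months of intervention". Depending on the type of variable, t tests, "chi-square tests of cluster summary measures, or multivariate analyses will be applied". Cluster-level summaries are to be compared, and "A random effects model will be applied to control possible confounders in individual and cluster levels". The confounders are not listed and none of these analyses is called primary.

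On baseline, Primary Outcome says the CBI will "measure the family caregiver’s burden at baseline (month 0) and then again at month 6". The section on screening and assessment of family burden, which includes the CBI, adds: "The results will be utilized as a baseline assessment from which to measure the overall impact of the CIIC center".

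On allocation, Study Setting assigns "sub-district XXX (10 villages) for intervention and subdistrict YYY (15 villages) for control". Sequence Generation explains that villages in different municipalities cannot be randomised to arms. The random draw only selects six villages inside each municipality.

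On imbalance, Challenges and Limitations concedes: "Cluster randomization may increase the risk of imbalance in the 2 arms at baseline". The planned response is a check of aggregate baseline summaries, with no stated consequence for the analysis.

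**The concern.** When units are randomised to arms, a comparison of follow-up values alone is unbiased, and baseline adjustment mainly buys precision. Here the arm is fixed by subdistrict. Random selection of villages within a subdistrict makes them representative of it, but does nothing to make the two subdistricts alike. Any true difference in caregiver burden between them at month 0 that persists to month 6 is counted as intervention effect, in either direction.

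The open list of analyses adds to this. CBI is one summed score, so at least two analyses remain available for it: a t test on village summaries and a random effects model, each with or without baseline. If their results differ, the text does not say which one is judged against the single 0.05 threshold.

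**Working it through.** **Inputs from the protocol article (Sample Size).** Target difference 0.5 unit; SD 4; significance level 0.05; design effect 1.2; loss up to 20%; 2000 participants and 6 villages per arm. Power and sidedness are not stated.

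**The plan's own figure.** Assume 90% power, two-sided.
- n per arm = 2 × (1.960 + 1.282)² × 4² / 0.5² = 1345.
- × 1.2 = 1614; ÷ 0.80 = 2018 per arm, or 4036 in total.

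This is within 1% of the stated 4000. The match is not unique: one-sided 95% power with dropout added as a multiplier gives 3994. Either way, the trial is sized for 0.5 / 4 = 0.125 SD, so a small gap between subdistricts matters.

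**Standard error on the plan's terms.** Effective n per arm = 2000 × 0.80 / 1.2 = 1333. SE = 4 × √(2 / 1333) = 0.155.

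**Bias of an unadjusted month-6 contrast.** Let g be the baseline CBI gap between subdistricts and r the share of it still present at month 6 without any intervention effect. Bias = r × g. Both are assumptions. False-positive rates use a t test on 10 df (12 villages − 2) with SE 0.155.

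| g | r | Bias (units) | Share of 0.5 target | False-positive rate |
|---|---|---|---|---|
| 0.5 | 0.3 | 0.15 | 30% | 14% |
| 0.5 | 0.5 | 0.25 | 50% | 31% |
| 0.5 | 0.7 | 0.35 | 70% | 53% |
| 1.0 | 0.5 | 0.50 | 100% | 83% |

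**What baseline adjustment does.** A model with baseline CBI subtracts b × g, where b is the within-arm slope of month-6 on baseline CBI. The remaining bias is (r − b) × g, plus any subdistrict difference that does not act through baseline CBI. With b = 0.5 assumed and g = 0.5:
- r = 0.3 leaves (0.3 − 0.5) × 0.5 = −0.10;
- r = 0.5 leaves 0;
- r = 0.7 leaves +0.10.

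The bias shrinks but is not guaranteed to vanish. With one subdistrict per arm, the data cannot show how much is left.

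**The case against.** The strongest reply is that the plan does not exclude baseline CBI. The random effects model is meant to handle confounders at both individual and cluster level, and baseline CBI is an obvious candidate. The screening section treats the month-0 assessment as the reference for measuring impact. A covariate list and a degrees-of-freedom method are details that an article may leave to a full protocol or analysis plan. This stands: it cannot be said that the trial will ignore baseline CBI, nor that a baseline gap carries over in full. It does not settle the point, because the published text itself words the primary contrast as month-6 values and sets out several analyses without ranking them.

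A reader might infer four stronger criticisms that the documents do not support.

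- **A chi-square test is planned for the continuous primary outcome.** The list is qualified by the type of variable, and the chi-square option may be meant for categorical outcomes.
- **The mixed model will have inflated type I error from normal-based inference with 12 villages.** No such inference is specified, and the planned comparison of cluster summaries is itself a small-sample method.
- **Chance differences between villages make a 0.5-unit baseline gap likely.** Assumed intracluster correlations of 0.01-0.05 give 6-35%, but the protocol's design effect of 1.2 implies about 0.2 / 266 = 0.00075. The SE is then √(32 × 1.2 / 1602) = 0.155, and the chance of a gap above 0.5 is about 0.1%. Chance gaps between villages are also already in the standard error of a village-mean test. The bias at issue comes from a true subdistrict difference.
- **Adjustment would remove most of the bias.** Arm and subdistrict are fully confounded, so this cannot be shown.

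**Conclusion.** The point holds as a weakness in how the primary analysis is fixed. The text leaves a t test, a cluster-summary comparison and a random effects model side by side, and gives baseline CBI no stated role in any of them. In this design an unadjusted month-6 comparison is exposed to any persisting difference between the two subdistricts.

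The size is illustrative. A 0.5-unit gap with 30-70% persistence gives a bias of 0.15-0.35 unit against a 0.5-unit target. It rests on the assumed gap and persistence, neither of which the documents supply. The false-positive rates also rest on the protocol's design effect of 1.2; a larger design effect would widen the standard error and lower them, without changing the bias. Baseline adjustment is the better primary method here, but it does not turn the comparison into one between randomised arms.

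**What to change.** Before the analysis is run, name one primary analysis of CBI: a linear mixed model of month-6 CBI on arm, with individual baseline CBI as covariate, a village random intercept and a small-sample degrees-of-freedom method such as Kenward-Roger or Satterthwaite. A baseline-adjusted t test on village means is an acceptable alternative. Keep the unadjusted village-mean t test as a sensitivity analysis, and list any further covariates in advance.

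Add a sentence saying that arm and subdistrict are fully confounded, and that adjustment for baseline CBI reduces this confounding but cannot remove it.

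The cost is wording: month-0 CBI is already part of data collection and the sample size does not change. If village-mean baseline CBI is also entered, it uses one of the 10 village-level degrees of freedom.

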#### Secondary Outcomes

Secondary outcomes consist of biopsychosocial indicators including ADL, depression, and QOL of older people, which will be compared between intervention and control groups.

Functional ability will be assessed by applying the Barthel Index for ADL assessment [16], which measures the level of ability for 10 basic items (bowel movement, incontinence, grooming, toileting, feeding, transfer, mobility, dressing, stairs, bathing). Total possible scores range from 0 to 20, with lower scores indicating increased disability.

Depression will be screened by applying the Geriatric Depression Scale (GDS), which is internationally commonly used, validated, and regularly used in Thailand [17].

Health-related QOL will be measured with the EQ-5D-5L questionnaire [18] using the EQ visual analogue scale (EQ VAS) [18,19]. A validated Thai version of the instrument is already available and will be used after piloting. The EQ-5D-5L measures 5 dimensions with 5 levels: mobility, self-care, usual activities, pain/discomfort, and anxiety. The EQ VAS is a measure of overall self-rated health status with a vertical VAS where the end points are labeled “Best imaginable health state” and “Worst imaginable health state.”

Cost for the intervention will be calculated in terms of intervention cost, family cost, and community cost. The details of the intervention cost will inform the estimated cost when expanding the area covered by the CIIC services.

The first possible outcome of the implementation of the CIIC intervention is promoting the capacity of the family caregivers through technical training, early detection of dependency problems, and respite care when the caregiver is overburdened in addition to linking families and primary health care services. The intervention components such as the (1) community respite home and (2) technical capacity building of the caregiver are directly targeting the reduction of caregiver burden.

Therefore, we set caregiver burden as the primary outcome of the study. ADL is also an important outcome of the component. Although we set these as the primary and secondary outcomes, respectively, in terms of the research methodology, they are both important outcomes of the study.

Selecting an outcome that is directly related to most of the intervention practically, we chose caregiver burden as the primary outcome. In a country with an FLTC system as its backbone, this outcome is more practical.

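### The MANOVA named for the secondary outcomes has no stated village term; run on individuals, it would exceed 5% type I error even at the protocol's own design effect

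*Protocol article*

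**What the plan says.** The Statistical Methods section of the protocol article opens with a sentence about outcomes in general: "Outcomes will be compared between intervention and control clusters after 6 months of intervention". The next paragraph begins with the primary outcome, the Caregiver Burden Inventory (CBI). It contains the statements "Cluster-level summary statistics will be compared" and "A random effects model will be applied to control possible confounders in individual and cluster levels". A short paragraph on the complex intervention then says that "a village as a random effect is due to population and social economic status", without tying this to any particular outcome.

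The secondary outcomes have a separate paragraph. For ADL, GDS and EQ-5D-5L it states that "the analyses will compare the 2 arms by applying a multivariate analysis of variance model". No other sentence assigns a method to these outcomes by name, and this one mentions neither villages nor the unit of analysis.

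The Trial Design section makes the village the unit of randomization. The Sample Size section gives 6 clusters per arm, 300 to 350 people per cluster, a design effect of 1.2 and up to 20% loss. It gives no ICC.

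**The concern.** A standard MANOVA assumes independent observations. People in one village share services, volunteers and, in the intervention arm, group exercise classes, and the protocol itself treats the village as a random effect. If up to 4000 people are entered as independent, the standard errors omit the between-village component. Ordinary differences between villages can then appear as an effect of the intervention.

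The result of a MANOVA is also a single joint P value. The Hypothesis section names functional ability and quality of life separately. The Secondary Outcomes section says of caregiver burden and ADL that "they are both important outcomes of the study". A joint P value does not say whether ADL, depression or quality of life moved, or by how much. At stake are false or uninterpretable claims about the older people themselves, as opposed to their caregivers.

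**Working it through.** **Inputs from the protocol article.** 6 villages per arm; 2000 people per arm, so 2000/6 = 333 per village, or 333 × 0.8 = 267 after 20% loss; design effect (DE) 1.2; significance at P<.05, taken as two-sided.

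**Assumptions.** Three outcomes, one score per instrument. The design effect of 1.2 applies to the secondary outcomes as well; the protocol gives only one. ICCs of 0.005 and 0.01 are illustrative, since the protocol gives none. The simulation uses a correlation of 0.4 between outcomes.

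**The plan's own figure.** For a difference of 0.5 with SD 4, n per arm = 2 × (1.960 + 1.282)² × 4²/0.5² = 1345 at 90% power. Power is not stated, and 90% is the value that fits. Then 1345 × 1.2 = 1614, and 1614/0.8 = 2018 per arm, or 4036 in total, within 1% of the stated 4000. The factor of 1.2 is therefore consistent with the planned size.

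**ICC implied by 1.2.** From DE = 1 + (m − 1) × ICC: 0.2/332 = 0.0006 at m = 333, and 0.2/266 = 0.00075 at m = 267.

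**Type I error if villages are left out.** The true variance of the arm difference is DE times the variance that the test assumes. Hence:

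- one outcome: 2 × [1 − Φ(1.960/√DE)]
- joint test of three outcomes: P(χ² on 3 df > 7.815/DE)

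At DE = 1.2: 1.960/√1.2 = 1.789, giving 7.4%; and 7.815/1.2 = 6.51, giving 8.9%.

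| People per village | ICC | DE | One outcome | Joint test |
|---|---|---|---|---|
| protocol's design effect | 0.0006–0.00075 | 1.20 | 7.4% | 8.9% |
| 267 | 0.005 (assumed) | 2.33 | 19.9% | 34.0% |
| 333 | 0.005 (assumed) | 2.66 | 22.9% | 40.1% |
| 267 | 0.01 (assumed) | 3.66 | 30.6% | 54.5% |
| 333 | 0.01 (assumed) | 4.32 | 34.6% | 61.3% |

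**Check by simulation.** With no effect, 6 + 6 villages of 267 and 3000 runs per setting, the two-group MANOVA (Hotelling T²) on individuals rejected in 8.9%, 33.1% and 54.5% of trials at ICC 0.00075, 0.005 and 0.01. This agrees with the formula. The same MANOVA on the 12 village means (F on 3 and 8 df) rejected in 5.3%, 4.9% and 5.1%. So the unit of analysis causes the inflation; the multivariate method does not.

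**The case against.** The strongest reply is that the section does not say the MANOVA is run on individuals or that villages are left out. Its first sentence speaks of clusters and covers all outcomes. Cluster summaries are planned. The paragraph on the village random effect is not confined to the CBI and stands directly before the secondary-outcome paragraph. A MANOVA on village means would be valid. An article may also leave to the full protocol or SAP how the MANOVA is combined with the village effect, which covariates enter, and how each outcome is followed up.

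Much of this stands. A reader might infer that the plan definitely ignores villages; the text supports only that it does not say how they enter. A reader might also infer that false-positive rates will be far above 5%. That needs an ICC the document does not give: at its own design effect the error is 7% to 9%. The missing baseline term in the MANOVA sentence is not an error in itself, and the rule of P<.05 with 95% confidence intervals shows that intervals are foreseen.

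What the reply does not remove is that the article goes beyond silence. It gives the secondary outcomes a named method of their own, apart from the random effects model, and in standard form that method has no place for the village. Someone following the text literally could run an invalid test.

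**Conclusion.** The point holds as a defect in how the secondary analysis is fixed. The named MANOVA has no stated village term and no explicit link to the clustered methods elsewhere in the section. If run on individuals, its joint type I error is about 9% at a design effect of 1.2. It rises to about 34% to 61% at ICCs of 0.005 to 0.01, which are assumptions and not protocol figures. Even a small ICC matters with about 300 people per village. If run on village means, the error is about 5%.

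These figures treat villages as exchangeable between arms under the null. They say nothing about differences between the two subdistricts, each of which supplies one whole arm.

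This should be fixed, but it is not critical: the outcomes are secondary, the text allows a valid reading, and the primary analysis is not affected.

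**What to change.** Replace the MANOVA sentence with one model per secondary outcome: the month-6 value on arm and baseline value, with a village random effect and small-sample degrees of freedom. A simple equivalent is to compare baseline-adjusted village means with a t test on about 12 − 2 = 10 df. Report each adjusted difference with its 95% CI. If a joint MANOVA is kept, state that it is run on village means.

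The Data Collection and Follow-Up section implies that all secondary outcomes have a baseline value. The description of the baseline screening lists ADL and EQ-5D-5L but not GDS, so confirm that baseline GDS is collected before writing it into the model.

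The change affects analysis wording only and uses a village effect the section already accepts. The cost is wider intervals. Relative to an analysis that takes no account of villages, and before any gain from baseline adjustment, the widening is about √1.2 × 2.228/1.960 = 1.25 times at the protocol's design effect. At design effects of 2.33 to 4.32 it is about 1.7 to 2.4 times by the same formula. The change does not remove confounding from each arm being a single subdistrict, and the report should say so.
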